### Statistical analysis

2.9

The power of the test is 80% and α = 0.05. According to the literature, the incidence of esophageal cancer perforation after re-irradiation is 30%. It is expected that after re-irradiation with PLDR technology, the rate of esophageal perforation will decrease to 10%. The optimal sample size for re-irradiation is 27 cases by checking the table (β = 0.20, α = 0.05).^[19]^ The proportion of patients with clinical response and the 95% confidence intervals will be calculated and reported. The Chi-Squared test and Kaplan–Meier method will be used to analyze the rates and severity of disease progression according to NCI-CTCAE (version 4), and Fisher exact probability test will be used to analyze the correlations between clinical outcomes and toxicity.

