### Recruitment and study design

2.1

This study is a prospective, multi-center, open, single-arm phase II clinical trial designed to enroll 27 patients with locally recurrent ESCC after radiotherapy with or without chemotherapy (Fig. 2). Before the start of treatment, each eligible patient will be fully explained the ethics, purpose, design, implementation, requirements, and timing of the study.

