### Assessment of the primary and secondary endpoints

2.8

Rate of esophageal perforation is the primary endpoint in this study, which will be observed from the initiation of re-irradiation to 60 days after the end of the study. Esophageal perforation should be diagnosed by esophageoscope. ORR is one of the secondary endpoints in our study. Ninety days after the end of treatment, we will evaluate the efficacy by using the RESICT 1.1 criterion through CT scan and esophageoscope. Quality of life scale QLQ-C30 (V3.0) according to the European Organization for Cancer Research and Treatment (EORTC) and digital pain scale will be assessed to determine the palliative effect on quality of life and pain in 2 years after the end of the study. Kaplan Meier curves will be performed to evaluate TTP, 2 years after the end of the study.

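### The 27 patients match an optimal two-stage design, but the article describes one enrolment with no stages or cut-off; in a single stage, 27 cannot give both alpha 0.05 and 80% power.

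*Protocol article*

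**What the plan says.** The Statistical analysis section (2.9) opens with the error rates: "The power of the test is 80% and α = 0.05". It takes from the literature that "the incidence of esophageal cancer perforation after re-irradiation is 30" per cent, and expects that with the pulsed technique "the rate of esophageal perforation will decrease to 10" per cent. The sample size is then read from a cited table, at beta 0.20 and alpha 0.05: "The optimal sample size for re-irradiation is 27 cases by checking the table".

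Recruitment and study design (2.1) calls the trial a "prospective, multi-center, open, single-arm phase II clinical trial designed to enroll 27 patients", and the abstract says the same in similar terms. Section 2.8 confirms that "Rate of esophageal perforation is the primary endpoint in this study".

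None of these places mentions a first stage, an interim look, a rule for continuing, or the number of perforations at which the trial would be called positive. Section 2.9 does not say whether alpha is one- or two-sided. The analyses it lists concern clinical response, disease progression, and the correlation of outcome with toxicity. It names no test of the perforation rate against 30%.

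**The concern.** The words for optimal size and for a table look-up suggest a published two-stage phase II table. In such a design the final cut-off keeps its alpha only because some trials stop at the first stage. If the total is borrowed and the first stage is not used, the quoted alpha and power no longer apply.

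The stake is how the primary result will be read. With 27 patients in one stage, the choice between 3 and 4 as the largest acceptable number of perforations decides whether a result of exactly 4 counts as success. It also decides whether the power is below 80% or the alpha above 0.05. The article fixes neither the design nor the cut-off, yet states both error rates as facts.

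**Working it through.** **Inputs (section 2.9).** Perforation rate 30% under the null and 10% under the alternative; alpha 0.05; beta 0.20. Sidedness is not given. One-sided 0.05 is assumed first, and 0.025 per side is tried as well.

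**Step 1: reproduce 27.** Two-stage designs were enumerated exactly, with n1 patients first, continuation if at most a1 perforate, and success if at most a perforate among all n:

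P(success | p) = sum over k = 0 to a1 of P(X1 = k | n1, p) × P(X2 ≤ a − k | n − n1, p).

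The design with the smallest expected size under 30% has n1 = 6, a1 = 1, n = 27, a = 4:

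- Alpha, p = 0.30: 0.1176 × 0.1984 + 0.3025 × 0.0856 = 0.0233 + 0.0259 = 0.049.
- Power, p = 0.10: 0.5314 × 0.9478 + 0.3543 × 0.8480 = 0.5037 + 0.3004 = 0.804.
- Probability of stopping at the first stage under 30%: 1 − (0.1176 + 0.3025) = 0.58.
- Expected size under 30%: 6 + 21 × 0.42 = 14.8.

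So 27 is reproduced exactly.

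**Step 2: other methods on the same inputs.**

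| Method | n |
|---|---|
| Two-stage, smallest expected size, alpha 0.05 | 27 |
| Two-stage, smallest maximum size (minimax) | 26 |
| Exact single-stage, one-sided 0.05 | 28 |
| Normal approximation, one-sided (25.3) | 26 |
| The same with continuity correction | 31 |
| Arcsine, one-sided | 24 |
| Normal, two-sided / with correction / arcsine | 34 / 38 / 30 |
| Exact single-stage, 0.025 per side | 31 |
| Two-stage, smallest expected size, alpha 0.025 | 35 |

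The one-sided normal figure is [(1.645 × √0.21 + 0.842 × √0.09) / 0.20]² = 25.3. Only the first row gives 27, although several methods come within one patient of it.

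**Step 3: 27 patients in one stage, exact binomial.** Alpha = P(X ≤ c | 27, 0.30) and power = P(X ≤ c | 27, 0.10):

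| Success if perforations are at most | Alpha | Power |
|---|---|---|
| 3 | 0.0202 | 0.718 |
| 4 | 0.0591 | 0.873 |

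A lower cut-off loses more power and a higher one raises alpha further, so no cut-off meets both targets. At 0.025 per side, 3 is again the largest allowable cut-off, because 0.0202 is below 0.025 and 0.0591 is not. Power is the same 71.8%.

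**Step 4: the nearest single-stage size that works.** With 28 patients and at most 4 perforations, alpha is 0.0474 and power 0.858. Both one-sided targets are met.

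**Step 5: would a first-stage look fit the endpoint window?** Section 2.8 observes perforation from the start of re-irradiation until 60 days after the end of the study. Read literally, the endpoint is not complete for any patient before the study ends, so no interim look could use complete data. If the end of treatment is meant, and fractions are given five a week (an assumption), 25 fractions take about 35 days. The last first-stage patient would then be complete after about 35 + 60 = 95 days. Section 2.12 plans one year of recruitment.

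**The case against.** The strongest reply is that nothing stated is numerically wrong: 27 follows exactly from the stated inputs as an optimal table entry. This is a condensed article. The figure showing the trial plan, the cited table and the full protocol are not shown, and the stages may be set out there. The article never calls the trial single-stage; that reading rests on its silence about stages. On that reading the shortfall is one patient.

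Much of this stands, and it limits the point. Four stronger conclusions might be inferred that the documents do not support:

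- That the first stage was dropped. The article does not say so, and its wording also fits a two-stage design reported in brief.
- That alpha is in fact exceeded. The 5.9% arises only with a cut-off of 4 in a single stage, and the article adopts no cut-off.
- That 6 then 27 is certainly the source. It is the best match, but other 27-patient designs also meet both limits. For example, 12 first, continuing with at most 2 perforations and succeeding with at most 4 in all, has alpha 0.0495 and power 0.822; its expected size is 15.8 against 14.8.
- That all 27 patients would be treated whatever happened. Section 2.11 places the trial under ethics committee supervision. That is not a statistical boundary, but an unprinted boundary does not show that there is no oversight.

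The reply does not rescue the positive claim of 80% power and alpha 0.05. Those figures are stated without condition beside a description of one enrolment of 27, and for a single stage they cannot both hold.

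**Conclusion.** The point holds as a mismatch between the stated error rates and the design described, not as an error in the headcount. The inputs give 27 exactly, among the methods tried, only as the total of the optimal two-stage design, with alpha 4.9% and power 80.4%. If the trial is single-stage with one-sided alpha 0.05, either power falls to 71.8%, which is 80 − 71.8 = 8.2 points short, or alpha rises to 5.9%. At 0.025 per side the power is also 71.8%. If the trial is two-stage, the figures are right and the description in the abstract and in sections 2.1 and 2.9 is incomplete on a basic design feature.

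The binomial results are exact. The single-stage reading, the one-sided alpha and the identity of the table entry are assumptions or inferences.

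**What to change.** Reconcile the abstract, section 2.1 and section 2.9. State whether the design has one or two stages, whether alpha is one- or two-sided, and how many perforations count as success. Give the alpha and power that belong to that design.

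- If single-stage at 27: restate as success with at most 3 perforations, alpha 2.0%, power 71.8%. This costs wording and a less favourable stated power. Alternatively, 28 patients with success at 4 or fewer perforations meets both one-sided targets, at the cost of one patient.
- If two-stage was intended: report the stages and boundaries actually taken from the cited table, and reconcile the first-stage look with the perforation window in section 2.8. This is wording, but the observation window may make the wait before the look substantial, and section 2.12 says recruitment opened in February 2019. Whether to adopt any stopping rule, and which, is for the investigators.

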### A quality assurance

2.10

IMRT-PLDR QA group will be established with 2 radiation oncologists and 1 physicist.

### Ethics and dissemination

2.11

This trial was approved by the Ethics Committee of Mianyang Central Hospital, Sichuan Province, China with trial number: S2018071. The trial is subject to the supervision and management of the ethics committee. Written informed consent is obtained from all participants.

### Trial status

2.12

The clinical registration was approved on January 10, 2019, This study opened to recruitment in February 2019, with a planned recruitment period of 1 year.

## Discussion

3

Currently, there is no standard treatment available for local recurrence after radiotherapy. Numerous basic research studies reveal low-dose rate radiation to be effective to alleviate the side effects of radiotherapy. Based on the effects of low dose radiosensitivity and low dose hyperrepair, we designed IMRT-PLDR radiotherapy for local recurrence of ESCC after radiotherapy.

This study is novel in testing the safety and efficacy of PLDR for the treatment of locally recurrent ESCC. Our expected results are that PLDR causes fewer side effects and offers effective treatment, when compared with the historical data of conventional radiotherapy. The study results will indicate more treatment options for locally recurrent ESCC.
